### Setting and Participants

The study will be conducted in five Northeast, Central, and South-central Pennsylvania nursing homes that provide rehabilitation services (post acute/skilled nursing care). Sites were selected to ensure a large population for recruitment and to increase the diversity of the sample. To improve the potential for translation into practice and to increase the generalizability of our findings we have selected a mix of for-profit, nonprofit, county-owned, rural and urban, and large, medium, and small community-based settings.

Participants are individuals with DSD who are admitted to post-acute care following hospitalization. These individuals will meet the following inclusion criteria: age 65 years or older; English speaking; community residing prior to hospitalization; diagnosis of mild to moderate stage of dementia as confirmed by medical chart review and/or a score of 0.5 to 2.0 on the Clinical Dementia Rating Scale[82]and a score of 3 or greater on the Modified Blessed Dementia Rating Scale[83]; and at least two features of delirium as assessed by the Confusion Assessment Method. A consensus panel of three members with expertise in geriatric medicine, neuropsychology, and delirium will adjudicate all dementia and delirium diagnoses. Exclusion criteria include: severe hearing, speech or vision impairments; medical diagnoses of acute major depression, acute psychiatric condition, acute stroke, Parkinson's disease, Huntington's disease, normal pressure hydrocephalus, seizure disorder, subdural hematoma, head trauma, or known structural brain abnormalities; or a life expectancy of less than 6 months. Participants who satisfy all enrollment criteria will be invited to participate in the study.

### Consent Process

Participants in this study will be frail older adults who lack decisional capacity due to their delirium superimposed on dementia. Participants and their legally authorized representative (LAR) will be approached for screening and consent (for those found eligible) at the point of admission to post-acute care. The LAR will sign for the participant and a copy of the consent will be given to them. We ask the participant for assent on a daily basis prior to assessment and intervention.

### Randomization and Control of Cross-Contamination

Randomization will be concealed until after the initial screen and consent are obtained and an ID number is assigned to the participant. The statistician will generate the randomization sequence using a random number generator. Randomization will be conducted in blocks by nursing home site and time to ensure equal assignment across the two groups at the completion of the study and approximately equal assignments throughout the study to control for unknown temporal effects. The statistician will be blinded to treatment coding.

Our team discussed several randomization procedures and we have elected to randomize by participant rather than by site, even though the latter approach is an excellent method for controlling cross-contamination of conditions. There are several reasons for our decision. First, nursing homes are unstable environments[84] and there is evidence indicating that nursing home quality indicators are unstable from one six-month period to the next[85]. Changes in quality indicators may reflect change in quality of care and/or resident profile. Either could potentially impact our outcomes because of their likely effect on usual care. Second, we are confident that we can control treatment contamination within sites, and for the same sample size, randomization by participant will provide greater power than randomization by nursing home.

We control for cross-contamination by conducting all interventions using our trained research assistants (RAs) (not nursing home staff) in an area specifically set aside for these sessions. Nursing homes have provided us with this research space in the past and staff has always respected our procedures for control of cross-contamination. Only the resident scheduled for a particular session will be allowed access to the area for that time period.

### Intervention

Participants in the intervention group will receive nursing care that is routinely delivered for their medical/surgical condition including participation in their prescribed therapies plus RESERVE-DSD. This intervention consists of increasingly challenging recreational activities that are cognitively stimulating and tailored to each participant's interests and functional abilities. The recreational activities target cognitive functions affected by delirium: attention, orientation, memory, abstract thinking, and executive functioning. Participants will receive up to 30 minutes of their respective recreational activities once a day between the hours of 1 pm and 5 pm for up to 30 consecutive days beginning within 24 hours of admission to post acute care.

The cognitively stimulating recreational activities to be studied are from previously designed, well-established programs of therapeutic activities from [name]'s research on the behavioral and cognitive symptoms of dementia, respectively. We have constructed a large base of cognitively stimulating recreational activities, many taken from the growing literature on brain fitness[75,86-90]. The activities, such as word search, finish the phrase, and name that tune, offer stimulation in multiple cognitive domains, combined in novel ways, as opposed to stimulation in a single cognitive domain like memory training.The investigators have classified the base of recreational activities by most prominent domain stimulated, however, in actuality activities stimulate several cognitive domains simultaneously. For example, the game of "Name that Tune" requires processing in the areas of both attention and memory. Multi-domain cognitive activities demonstrate more robust results than single domain training[91]. The activities are implemented using inexpensive items and are readily available to most nursing homes. Because they require no special expertise to implement, they are well-suited to the resource-stressed nursing home environment.

#### Assessment and Prescription

The selection of activities for each participant will be determined by [name]. Each participant's baseline data, including dementia stage, physical function, and activity interests are reviewed. Based on this assessment, three recreational activities tailored to the participant's functional abilities and designed around themes of their interests will be selected by level of difficulty (easy, moderate, and hard) in each cognitive domain. For example, a participant who has arthritic problems with their hands, a mild stage of dementia, and a history of interest in gardening might be prescribed: identify the sound of a lawn mower (attention); discuss whether the current calendar month is good for planting (orientation); memory tray with three or more garden tools (memory); describe steps to planting a garden (abstract thinking); and having the participant plant flower seeds using adapted hand tools (executive functioning). Using the domain of attention as an example, increasing the level of difficulty might proceed in this fashion: lawn mower sound identification (easy); circle the garden tools in a picture (moderate); item search of vegetables embedded in a "busy" picture (difficult). We provide variety from day to day to encourage cognitive processing and to prevent a practice effect.

#### Procedure for Implementation

To encourage initial engagement in the activity, the research assistant (RA) will use the System of Least Restrictive Prompts[92] beginning with verbal cueing, followed by verbal cueing and demonstration of the activity. Participants are then encouraged to read out loud, point out facts, work puzzles, ask questions, answer questions, or make choices. RAs will use principles for implementing cognitive activities outlined by Green & Bavelier[93]: active engagement, incremental increases in task difficulty; verbal encouragement and motivation throughout the session; feedback and praise; and variability in tasks. These approaches maximize cognitive processing and restoration.

#### Scheduling and Duration of Intervention

Participants will receive the intervention for 30 minutes each day for up to 30 consecutive days between the hours of 1 pm and 5 pm. This dosage is based on a consensus report of activity effectiveness compiled by expert recreational therapists from the American Therapeutic Recreation Association and the National Recreation Society[94], standard recreational therapy practice in the nursing home, and studies that have demonstrated the efficacy of daily, 30-minute recreational therapy for behavioral symptoms and functional impairment in persons with dementia[95-97].

#### Treatment Fidelity

We use several methods to monitor and enhance the reliability of our intervention[98,99]. Intervention RAs are trained in a two-day program that we have developed, standardized, and used for many years to prepare RAs for implementing recreational activities with people who have dementia. These RAs need no special educational background because the activities we use are simple, non-technical games, and exercises. RAs will practice in simulated situations until they achieve 100% agreement on all critical elements of activity intervention before going into the field. The project director (PD) will monitor delivery of the treatment by observing each RA conduct interventions on 10% of sessions in the field (randomly selected). Retraining will be initiated if treatment fidelity is not obtained, as assessed by any "no" answer on the treatment fidelity checklist. Additionally, RAs will complete a treatment fidelity check for any intervention session that was not delivered according to protocol. We will monitor receipt and enactment of treatment using measures for participant adherence to the protocol: intervention dose (time on task and level of participation) and duration (number of treatment days received). Our methods and measures will help us to monitor and ensure the reliability of our intervention, its delivery, receipt and enactment.

### Description of Usual Care (Control)

At the present time there is no standard care for DSD [43,81]. Participants in the usual care group will receive nursing care that is routinely delivered for their medical/surgical condition including participation in their prescribed therapies. To describe what constitutes usual care (control) we will conduct medical chart reviews on all participants (intervention and control) and extract data on the following: attendance at prescribed therapies and activity programs; CNS-active drug use (regular and prn); and nursing interventions recorded for behaviors nurses use to describe delirium[100]: confusion, disorientation, altered mental status, agitation, inappropriate behavior, mental status change, inattention, hallucination, and lethargy. Because the nursing home environment is unstable[84,85], we will also record data every six months on staffing ratios at each site, as published on the Pennsylvania Department of Health website, and assess staff knowledge of delirium using our previously developed case vignettes[101]. We will ask all consenting staff (RN, LPN, and CNAs) to complete the vignettes at baseline and then every six months during data collection to capture any change in overall level of delirium knowledge per site that might occur due to historical factors or staff turnover in the nursing home. We will use these data to quantify usual care and to monitor any qualitative differences between sites.

### Measures

#### Baseline Measures

Following consent, the PD will collect baseline data on all participants. From the medical chart the PD will extract demographic data, all medical diagnoses, and all medications and therapies prescribed using an investigator-developed *Baseline Medical Chart Review Form*. For all chart reviews we will incorporate methods that help improve the precision of data abstraction[102,103].

To determine ApoE status, the PD will obtain buccal swabs from all participants using a procedure established by the Huck Institutes of Life Sciences Genome Core Facility (GCF) at Penn State. ApoE status will be determined by extracting DNA from the buccal swabs using a protocol optimized by the Institute of Psychiatry in London[104]. To identify the six ApoE genotypes comprising the ApoE *E2, *E3 and *E4 alleles, two single nucleotide polymorphisms (SNPs) will be assayed using the TaqMan Allele Discrimination method. Based on the distribution in the AD population, we expect that approximately 40-45% of our sample will carry at least one *E4 allele[105].

Assessment of participants' lifetime of complex mental activities, a measure of cognitive reserve, will be obtained by interviewing a knowledgeable informant using the *Lifetime of Experiences Questionnaire (LEQ*)[54] a reliable and valid instrument for assessing educational, occupational, and leisure lifestyle activities that are protective against cognitive decline. The LEQ consists of 42 items constructed around two dimensions: three life stages (young, mid, and late adulthood) and specific vs. non-specific mental activity in each stage. Scores are calculated for each stage and then summed for a total LEQ score. Higher scores indicate higher lifetime mental activity. The LEQ has an overall internal consistency of .66, test-retest reliability of .98 and is discriminate between older adults with high and low mental activity levels. Healthy older adults with higher LEQ scores have shown less cognitive decline over 18 months than those with low scores, independent of covariates[54].

Activity interests will be assessed for participants randomized to RESERVE-DSD by interviewing the responsible party using an adapted version of the *Farrington Leisure History Checklist*[88]. This checklist contains 150 recreational activities categorized by games, social, outdoor and cultural activities. These data will be used to adapt cognitively stimulating recreational activities around themes that match participants' interests.

#### Measures of Primary Outcomes

Our primary outcomes are: *1) delirium *(duration and severity), 2) *cognitive function*, and 3) *physical function*. Because delirium status fluctuates, and because cognitive and physical function also fluctuates with delirium status, we will take daily measures of these outcomes to capture the variability typical of DSD. Blinded RAs will collect outcome data. We will have two separate groups of RAs: one to implement the intervention and the other to conduct daily assessments. Daily assessments will be completed during the morning hours (9 am to 11 am) and the intervention will be implemented during the afternoon hours (1 pm to 5 pm) to ensure that there is no contact between the two groups of RAs

*Delirium *will be measured by a structured interview consisting of questions from the *Montreal Cognitive Assessment *(MoCA)[106] observation and the *Confusion Assessment Method *(CAM)[107]. The MoCA is a brief cognitive screening tool that demonstrates excellent sensitivity (90% and 100%) in MCI and early AD respectively, and specificity (87%). Content validity was established by the high correlation (.87) between the MoCA and MMSE. MoCA items on orientation, memory and language are used in the assessment of delirium. The CAM is a standardized screening algorithm allowing persons without formal training to quickly and accurately identify delirium. The CAM has four features: 1) acute onset and fluctuating course, 2) inattention, and either 3) disorganized thinking, or 4) altered level of consciousness[107]. A participant is scored as having subsyndromal delirium if they exhibit any two features and full delirium if they exhibit features one and two and either three or four[108]. The CAM was validated against geriatric psychiatrists' ratings using DSM-III-R criteria and has been shown to have a sensitivity between 94% and 100% and a specificity between 90% and 95%[107,109]. The CAM has also been validated in persons with dementia. Studies have shown the utility of a daily CAM in identifying delirium and its waxing and waning states[110]. Delirium will be recorded daily by RAs as present or absent; full or subsyndromal; hyperactive, hypoactive or mixed[111]. *Delirium Duration *will be calculated as total number of days with full or subsyndromal delirium. *Delirium severity *will be measured daily using the *Delirium Rating Scale *(DRS)[112],a 16-item clinician-rated scale validated in both delirium and dementia groups, and having good sensitivity, specificity and high interrater reliability (ICC 0.97). Scores range from 0 to 39; higher scores indicate greater severity.

*Cognitive Function *will be measured with several instruments that capture the cognitive domains affected by delirium: attention, orientation, memory, abstract thinking, and executive function. These domains are also affected in dementia, but previous studies have shown that as they improve, DSD resolves[22,80]. *Digit Span *(forward and backward) is a subtest of the Wechsler Adult Intelligence Scale (WAIS) and a classic measure of attention[113]. Participants are given increasingly longer sequences of digits to repeat initially forwards then backwards and receive a point for each correct sequence. The assessment ends when the participant misses two sequences in a row. The maximum possible score is 16 (forward) and 14 (backward). Higher scores indicate better attention and working memory. Median reliabilities reach .97 and .96 for forward and backward spans respectively[114,115]. *MoCA *items on orientation and memory will be used to measure those domains. The *Similarities test *of the verbal Wechsler Adult Intelligence Scales (WAIS) will be used to measure abstract thinking. The *Similarities test *has 18 items requiring the participant to describe how two given things are alike (ex., a hamburger and pizza). The Similarities test measures concrete, functional, and abstract thinking. The WAIS was revised to cover normative data for individuals 16-89 years old with strong reliability and validity reported. Reliability coefficients for the WAIS and *Similarities test *range from .93-.70 and test-retest reliability has been consistently in the .80s[116]. The *CLOX*[117] will be used to measure executive function. It is an easy to administer clock drawing task that elicits impairment in executive function and discriminates it from non-executive constructional failure. The *CLOX *has two parts: *CLOX 1*, a free drawing of a specified time, and CLOX 2, a simple copying task. Both steps are rated on 14 items with scores ranging from 0 to 15, higher scores indicate better executive function. The *CLOX *has an internal consistency of .82, interrater reliability of .94 (CLOX 1) and .93 (*CLOX 2*) and correlates strongly with measures of cognitive function in healthy and cognitively impaired older adults (MMSE and EXIT25).

*Physical Function *will be measured using the *Barthel Index *(BI)[118,119], a commonly used ordinal scale for assessing activities of daily living in patients receiving inpatient rehabilitation. The BI has ten items (seven for self-care and three for mobility) that are scored in steps of five points with a total score range of zero (totally dependent) to 100 (fully independent). The BI is a reliable indicator of functional ability in older adults when administered by face-to-face interview (ICC 0.89) and on testing by different observers (ICC 0.95-0.97)[118,120].

#### Measures of Moderators of RESERVE-DSD

At baseline we will collect data on potential moderators of the intervention: we will use the *Lifetime of Experiences Questionnaire (LEQ)*[54] to obtain a measure of baseline cognitive reserve; and we will obtain *buccal swabs *for DNA extraction to identify the six ApoE genotypes comprising the ApoE *E2, *E3 and *E4 alleles[104]. These measures are described under baseline measures.

#### Measures of Variables Affecting Vulnerability

Dementia stage, age, comorbidity, pain, infection, dehydration and CNS-active drugs. Measures of these variables will be obtained during screening (dementia stage: Clinical Dementia Rating Scale), following consent at baseline (age, comorbidities: baseline chart review), daily (presence of pain), and weekly (infection, dehydration and CNS-active drugs: weekly chart review). We will use the *Charlson Co-morbidity Index*, a weighted index that takes into account the number and seriousness of co-morbid diseases, to calculate a co-morbidity score for each participant[121]. Pain will be measured daily using the Pain Assessment in Advanced Dementia *(PAINAD*) scale which is an observational scale of five items (breathing, vocalization, facial expression, body language, and consolability). We use an observational rather than a verbal scale for greater reliability on days when participants experience greater severity of delirium. *PAINAD *is scored from 0-10 and has an internal consistency reliability of 0.50-0.65 and interrater reliability of 0.82-0.97[122,123]. Infection and dehydration will be identified as present or absent (yes/no) during the weekly chart review. The trained RA will review new medical orders, lab values and nurses notes for indicators of infection and dehydration. CNS-active drugs can further cognitive deterioration because of their potent anticholinergic properties[35,36]. We identify CNS-active drugs administered through a weekly chart review using the American Hospital Formulary Service drug classification[36]. We then calculate the anticholinergic burden associated with these drugs using the *Anticholinergic Cognitive Burden *(ACB) Scale[124,125]. The ACB is an expert based practical index that classifies the severity of a drug's anticholinergic activity on cognition using a scale of 1 (mild), 2 (moderate) and 3 (severe). Total ACB is calculated by summing the ACB scores of all regularly and prn scheduled drugs administered to the participant for that week. We will weigh the ACB score for each drug by days administered during that week before summing for the total ACB score.

#### Measures of Dosage and Satisfaction with Intervention

Intervention efficacy is often related to dose. During each intervention session, dosage will be obtained by the RA using a stop watch to time the minutes and seconds that the participant engaged in activities (*time on task*: 0 to 30 minutes). The RA also rates the *Level of Participation *using a scale developed by Kovatch and Magliocco for measuring extent of participation in recreational activities (an indicator of cognitive processing)[126]. Scores range from 0 to 3 with descriptors for each numerical rating (dozing, null, passive, active), higher scores indicate greater participation. In our work we achieved interrater reliabilities (ICC) of .99 for time on task and .83 for Level of Participation. Total dosage received will be calculated by weighing each daily time on task score by level of participation score and then summing across intervention days. We will use these data to conduct analyses of the effect of dosage on primary outcomes of the intervention. Activities attempted per cognitive domain are recorded daily.

Because we wish to improve the potential for translating our intervention into practice, we will use investigator-developed *Satisfaction Surveys *to assess staff, family, and participant reports of satisfaction with RESERVE-DSD. These brief surveys are collected at the completion of the 30-day intervention period or at discharge, whichever comes first. We will use these data to refine our intervention for a future effectiveness study.

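### Total dosage depends partly on days observed and on delirium severity, so its association with the primary outcomes should not be read as an effect of dosage

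*Protocol article*

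**What the plan says.** All references are to the protocol article.

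- **Exposure** (Measures of Dosage and Satisfaction with Intervention). Time on task is recorded at each session ("0 to 30 minutes") and participation is rated from 0 to 3. Total dosage is obtained by "weighing each daily time on task score by level of participation score and then summing across intervention days".
- **Intended use** (same section). "We will use these data to conduct analyses of the effect of dosage on primary outcomes of the intervention". The section opens by linking efficacy to dose.
- **Number of dose days** (Scheduling and Duration of Intervention). "Participants will receive the intervention for 30 minutes each day for up to 30 consecutive days". The satisfaction surveys are "collected at the completion of the 30-day intervention period or at discharge, whichever comes first", which implies that sessions stop at discharge if that comes before day 30. This is an inference; the text speaks of intervention days, not days of stay.
- **Outcome sharing that window** (Measures of Primary Outcomes). Delirium duration is "calculated as total number of days with full or subsyndromal delirium", with no division by days observed. The Statistical Analysis section has outcomes measured for at most 30 days.
- **Links between delirium, engagement and stay.** The Background names attention as the main deficit in delirium and says that unresolved delirium lengthens rehabilitation. The Discussion says that it stops patients engaging fully in therapy.
- **Protection of the main result** (Statistical Analysis). The primary analyses are by intent to treat, whatever the level of participation.

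**The concern.** Two determinants of the dosage score are also determinants of the outcomes.

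1. **Days observed.** Each extra day adds to the dosage sum and gives another chance to count a delirium day. This pushes the association towards apparent harm, most directly for delirium duration. If sicker participants also stay longer, it extends to severity.
2. **Severity.** A more delirious participant engages for fewer minutes and is rated lower, so low dosage is partly a consequence of the outcome. This pushes the association towards apparent benefit.

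The article calls the result an effect on the primary outcomes. A reader could take a dose-response gradient as support for efficacy, or a reversed gradient as evidence against it, when its sign depends on which path is stronger.

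**Working it through.** The article gives no figure for the dosage analysis, so there is nothing to reproduce. The check has an arithmetic part and a simulation part.

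**Arithmetic from the stated definition.** Maximum dosage over 30 days is 30 min × 3 × 30 days = 2,700. Over 10 days it is 30 × 3 × 10 = 900. A participant observed for 10 days can earn 900/2,700 = one third of the dosage, and can accrue at most 10/30 = one third of the delirium days, of someone observed for 30.

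**Simulation with an intervention effect of exactly zero.** The intervention arm has 256/2 = 128 participants, from the planned total and equal assignment. Everything else is assumed:

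- Daily severity is in standardised units: between-person SD 1, mean change −0.03 per day (SD 0.02), daily noise SD 0.7. A delirium day is severity above −0.3.
- Stay is log-normal with median 20 days and log-SD 0.4, limited to 5 to 30 days, or fixed at 30. Where stay depends on severity, the coefficient is 0.2 per SD on the log scale.
- Participation is centred at 1.8, falls by a slope *b* per SD of that day's severity, and is rounded to 0 to 3. Minutes are centred at 20, fall by 4*b* per SD, and are limited to 0 to 30. Both vary between persons and from day to day.
- Dosage = Σ(minutes × participation) over days observed.

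Each row has 1,000 runs. Cells give the mean correlation with dosage and the share of runs with two-sided p < 0.05. The adjusted columns allow for baseline severity and, where it varies, length of stay.

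| Scenario | Delirium days | Mean severity | Days, adjusted | Severity, adjusted |
|---|---|---|---|---|
| No links, all stay 30 days | 0.00; 3.8% | 0.00; 4.0% | 3.7% | 4.2% |
| Stay varies, unrelated to severity | +0.21; 69.6% | −0.06; 9.2% | 7.4% | 5.8% |
| Stay longer when sicker | +0.41; 99.7% | +0.22; 68.7% | 8.1% | 5.5% |
| *b* = 0.1, all stay 30 days | −0.19; 58.6% | −0.20; 64.1% | 22.8% | 30.0% |
| *b* = 0.25, stay varies, unrelated | −0.10; 16.8% | −0.39; 99.7% | 85.5% | 87.0% |
| *b* = 0.5, stay varies, unrelated | −0.31; 95.5% | −0.59; 100% | 100% | 100% |
| *b* = 0.25, stay longer when sicker | +0.11; 23.5% | −0.11; 22.7% | 80.6% | 82.2% |

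The first row shows that the method holds its level when neither path operates. Adjustment for stay and baseline severity repairs the stay path. It does not repair the participation path, because dosage follows each day's state and not only the baseline.

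**Other assumed inputs.** With stay of mean 20 and SD 6 days, capped at 30, the correlation with delirium days was +0.32 (97% of runs). It was +0.60 when stay lengthened by 3 days per SD of severity (100%). When participation instead fell by 4 minutes and 0.4 rating points per SD, it was −0.47 with delirium days and −0.80 with mean severity (100%). Under a further set of inputs, opposing paths cancelled for delirium days in some cases, leaving 3% to 5%.

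**Candidate remedies under zero effect.**

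- *Afternoon dose against next-morning score, adjusted for the preceding morning.* With half-day autocorrelation assumed at 0.5 or 0.8 and slopes of 4 minutes and 0.4 points per SD, this gave false benefit in 100% of 200 runs. With slopes a quarter as large it did so in 97.5% to 99%, and in 84% to 88% after within-person centring. Without a participation link the rate was about 5%.
- *Dose per session.* Once participation follows severity, this and the lagged regression still rejected in about 92% to 100% of runs.
- *Random assignment as instrument.* The estimate is (mean outcome, intervention − mean outcome, control) / (mean dosage, intervention − 0). The numerator is the randomised difference, so error stayed near nominal, at 5% to 8%.

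**The case against.** The strongest reply is that the article states no dosage model. It gives no regression, covariates, lag or scaling, and the Statistical Analysis section does not mention dose. The data referred to could include the per-session records as well as the total, and a condensed article may leave the model to a fuller document. That stands as far as the model goes. It does not remove the point, because the summed, participation-weighted exposure and the aim of estimating its effect are both fixed in the text. Per-session dose and ordinary covariate adjustment do not cure the participation path either.

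Other limits also stand:

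- The sizes rest on assumptions and move with them. The stay path is mechanical mainly for delirium duration; when stay was unrelated to severity, the rate for mean severity was only 9%.
- Dosage is not among the three aims or the abstract's hypotheses, and the Treatment Fidelity section treats it partly as monitoring of receipt. Nothing in the article says that the dosage result will support an efficacy claim.
- A reader might infer that giving a null session a rating of 1 is a scoring error. The documents do not support that. The rating multiplies minutes actually engaged, so such a session may add little, and the meaning of the category lies in a cited scale that is not at hand.

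**Conclusion.** The point holds in a limited form. As defined, total dosage shares its time window with delirium days and is partly a consequence of severity. An association with the primary outcomes can therefore appear in either direction without any intervention effect. Under the main set of assumed inputs, false-positive rates with any path active ranged from 9% to 100% before adjustment, against a nominal 5%.

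Two stronger readings are tempting. One is that the analysis will always show a dose-response under no effect. It need not: opposing paths can partly cancel (23% to 24% in one scenario) or cancel fully for one outcome (3% to 5% under other inputs). The other is that the trial's efficacy result is compromised. It is not, because the intent-to-treat comparison does not use dosage. This should be changed, but it concerns an ancillary analysis.

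**What to change.** Change the wording in Measures of Dosage and Satisfaction with Intervention, and in the analysis plan:

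1. Report total dosage descriptively. Present any association with outcomes within the intervention arm as descriptive and non-causal, and do not call it an effect of dosage.
2. If a dose-adjusted efficacy estimate is wanted, use random assignment as the instrument, with dosage zero in the control arm. State its assumption that assignment acts on outcomes only through the measured dosage. Because it rescales the randomised difference, it is not independent evidence of efficacy.
3. Do not present a next-morning lagged regression or a per-session dose as unbiased. The participant's state at the session can drive both engagement and the next score.

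No new data are needed. The cost is a less precise and less striking dose result.
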